### Strategies to improve adherence to interventions

Subjects will be regularly called back to the hospital for follow-up. They will undergo laboratory tests, and pictures of their surgical wounds will be taken with their agreement.

### Relevant concomitant care permitted or prohibited during the trial

This trial will not impose special requirements for care and interventions.

### Provisions for post-trial care

When the trial is completed, the subjects will receive standardised treatment in accordance with guidelines.

### Outcomes

#### Primary outcomes

Wound healing time, wound exudation rate, cure rate during 14 days postoperation, recurrence rate during 3 months and total cure rate. The wound is regarded as cured when the grafted skin survives, and the wound has epithelised completely. Wound exudation will be rated on the basis of the number of times dirty underwear or sanitary pads are changed during 1 day.

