## Introduction

### Background and rationale

Anal fistulas, which are common in colorectal diseases, affect approximately 1/10,000 of the normal population every year, according to Corson’s report [1]. A fistula is a pathological connection between two epithelialised openings. An anal fistula is a granulation tract between the anal canal or rectum and the skin around the anal verge. Approximately 80% of anal fistulas develop secondary to cryptogenic abscesses arising from infected anal glands, which can spread to other parts in many directions and represent chronic perianal sepsis conditions [1].

A series of surgical or nonsurgical therapeutic options for anal fistulas have been developed. Nonsurgical methods include antibiotics, anal fistula plugs and fibrin glue. Numerous surgical procedures are available and include two types: impairing or reserving the anal sphincter, such as laying the anal sphincter open, fistulotomy, fistulectomy, loosening or cutting the seton, ligating the intersphincteric fistula-tract, video-assisted anal fistula treatment and fistula-tract laser closure. However, the ideal surgical technique for anal fistula treatment should aim to deracinate the internal opening, which often leads to sepsis, and the granulation tract then promote postoperative wound healing while preserving sphincter function and anal continence because maintaining normal continence relies on the complex interaction of the anal sphincter and pelvic floor innervations [2]. Procedures for impairing and preserving anal sphincters in anal fistulas have postoperative recurrence rates of 0–65% and incontinence rates of 0–63%. In radical techniques that involve cutting additional anal sphincter muscles, the recurrence rate decreases, and the incontinence rate increases accordingly [3]. Laying simple and low anal fistulas open directly is relatively effective and safe and is widely accepted by surgeons [4]. Anal fistulotomy, which involves the division of pathogenic tracts, has been applied to treat subcutaneous and intersphincteric anal fistulas and has an excellent healing rate of over 90% [3, 5]. However, the risk of faecal incontinence increases with the extent of the division of the external anal sphincter [6–8].

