### Sample size

This study is a superiority trial. Our pretest showed that the average wound healing times of the graft and no-graft groups were approximately 15 and 25 days, respectively. We assume that no difference in efficacy exists among the three centres. Assuming a two-sided significance level of 0. 05 and power of 80% (*α* = 0. 05, *β* = 0. 2), the sample size is calculated as 47 (fixed model as $$n_{1} = n_{2} = \frac{{\sigma^{2} \left( {{\text{t}}_{\alpha } + t_{\beta } } \right)^{2} }}{{\delta^{2} }}$$) [11]. Considering a loss to follow-up of 10%, the sample size for each group is 52 cases, and the total is 104 cases.

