## Statistical methods

### Statistical methods for primary and secondary outcomes

SPSS 22. 0 (IBM, Armonk, NY, USA) software will be utilised for statistical analysis. *P* ≤ 0. 05 will be considered statistically significant.

The primary outcomes will be compared between groups by using Pearson’s chi-squared test. *t*-test, corrected *t*-test (equal variance not assumed), and analysis of variance for repeated measurements will be used for data analysis, and grade data will be assessed via Wilcoxon two-sample test.

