### Methods for additional analyses

The hybrid control will use multivariate logistic regression and odds ratio and 95% confidence interval estimation. Clinically significant variables from the univariate analysis will be included in the multivariate model. Goodness-of-fit will be evaluated through the Hosmer–Lemeshow test. Statistical analysis will be performed by using SPSS 22.0. A two-tailed significance level of 0.05 will be used for all tests. *P* < 0.05 will indicate statistical significance.

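### Five unranked primary outcomes are each tested at 0.05 with no stated success rule, so neither the nominal 5% level nor the 80% power describes the trial's overall decision

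*Protocol article*

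**What the plan says.** Under Primary outcomes, the protocol article names five: "Wound healing time, wound exudation rate, cure rate during 14 days postoperation, recurrence rate during 3 months and total cure rate". None is called the lead outcome. Secondary outcomes have their own section, so all five hold primary status.

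Under Statistical methods for primary and secondary outcomes, P ≤ 0.05 is the criterion for significance. The next paragraph begins "The primary outcomes will be compared between groups by using" and goes on to name tests, with no order among the outcomes and no rule for combining them. Methods for additional analyses adds: "A two-tailed significance level of 0.05 will be used for all tests".

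Under Sample size, the trial is a superiority trial. The calculation uses one outcome only: "the average wound healing times of the graft and no-graft groups were approximately 15 and 25 days, respectively". Its error settings read "Assuming a two-sided significance level of 0. 05 and power of 80" per cent. The result is 47 per group, raised to 52 per group (104 in total) for 10% loss to follow-up. Healing time is not named there as the sole or leading primary outcome.

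For room to improve, Background and rationale says that fistulotomy "has an excellent healing rate of over 90" per cent.

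**The concern.** The stated objective is to confirm the efficacy of the graft, but the article does not say which pattern of results across the five outcomes would confirm it. Two readings are open.

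- **Any one suffices.** The trial then has five chances at 0.05 to produce a positive primary result, and a chance finding on one outcome could be presented as confirmation.
- **All five are required.** The false-positive risk is then not inflated, but the trial needs adequate power on every outcome. It was sized on healing time only. Total cure starts from a high control rate by the article's own figure, which leaves little room for a detectable gain.

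Under neither reading do the 0.05 and 80% in the Sample size section describe the overall decision.

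**Working it through.** **Inputs from the protocol article.** Five primary outcomes; 0.05 two-sided per test; 47 evaluable per group; 80% power; healing time 15 versus 25 days, a difference of 10 days; fistulotomy healing above 90%.

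**Assumed inputs.** The correlations between the test statistics, and the event rates used for total cure and recurrence. The article gives neither. It supports only a control cure rate of about 90% or more.

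**1. The plan's own figure.** The 47 per group cannot be reproduced because no standard deviation is given. The usual two-sample formula, n = 2σ²(z₀.₉₇₅ + z₀.₈)²/δ², has (1.960 + 0.842)² = 7.85. With n = 47 and δ = 10 it gives σ = 10 × √(47 / (2 × 7.85)) = 17.3 days. The formula as printed lacks the factor 2 and would need σ = 24.5 days. The loss step is 47 × 1.1 = 51.7, rounded up to 52. The calculation uses one outcome and one test at 0.05.

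**2. Any-one reading.** With five independent tests at 0.05, the familywise error is 1 − 0.95⁵ = 1 − 0.774 = 22.6%.

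The outcomes are related: cure by day 14, for example, follows from healing time. A simulation of five equally correlated two-sided normal tests (1,000,000 draws) gave:

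| Assumed common correlation | Chance of at least one false positive |
|---|---|
| 0 | 22.6% |
| 0.3 | 20.9% |
| 0.5 | 18.3% |
| 0.7 | 14.9% |
| 0.9 | 10.2% |

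The bound under any dependence is 5 × 0.05 = 25%.

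**3. All-five reading.** Joint power cannot exceed the power of the weakest component. Power of Pearson's chi-squared test at two-sided 0.05 with 47 per group, by exact enumeration of two binomials:

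| Outcome | Assumed rates | Power |
|---|---|---|
| Total cure | 90% vs 98% | 41% |
| Total cure | 92% vs 98% | 27% |
| Recurrence | 10% vs 5% | 17% |
| Recurrence | 5% vs 1% | 14% |

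Under these rates joint power is at most about 14–17%. With 52 per group the four figures are 40%, 27%, 15% and 16%, so the conclusion does not change.

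**4. Cost of keeping five primaries.** Bonferroni uses 0.05/5 = 0.01 per test, and the familywise error is then 1 − 0.99⁵ = 4.9% under independence and at most 5% under any dependence. Healing time tested at 0.01 with 47 per group has about 59% power if σ = 17.3 days. Restoring 80% would take 70 per group, or 70/0.9 = 77.8, about 78 after 10% loss. Holm starts at 0.01 and is never less powerful than Bonferroni.

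**The case against.** **The analysis plan may settle it.** Test order, co-primary rules and corrections are often set there, and that plan is not shown. The sentence on the level for all tests stands under additional analyses, after logistic regression, so its reach to the primary comparisons can be argued. A 0.05 threshold also does not exclude a fixed test sequence, which uses 0.05 at each step. This has some force, but the article itself gives five outcomes equal primary status, and its section on primary outcomes independently sets P ≤ 0.05. A sequence chosen later would re-rank outcomes presented as equals. A correction would contradict the stated level.

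**Healing time is the lead outcome in practice.** The background, the choice of comparator, the discussion and the sample size all centre on it. That is true, and it makes the remedy natural, but the article does not formally give healing time that role.

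**Stronger readings that the documents do not support.** A reader might infer that the article promises a 5% familywise rate and breaks it. It gives only a nominal level per test and in the sample-size calculation. A reader might take 22.6% as the actual error rate. It is the independence value, and overlap among these outcomes probably makes the true rate lower. A reader might conclude that the trial is almost certain to fail if all five are required. That rests on the assumed rates: the article gives no fistulotomy recurrence rate beyond calling it low, and no expected cure rate with the graft.

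**Conclusion.** The point holds. As written, the article fixes five primary outcomes, a 0.05 criterion for each, and a sample size built on one of them, with no rule linking them. This is a choice the article makes, not a detail it leaves out.

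The size depends on the success rule. If any one outcome suffices, the familywise error is 22.6% under independence and about 10–21% at assumed equal correlations of 0.9 to 0.3. Even at 0.9 that is about twice the nominal level. If all five are required, the error is not inflated, but joint power is below 80%. How far below depends on the assumed rates for total cure and recurrence.

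The test of healing time taken by itself, at its own 0.05 level, is not affected by this point. The problem is what may be claimed from the five together.

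**What to change.** Name wound healing time as the single primary outcome at two-sided 0.05. Make exudation, 14-day cure, 3-month recurrence and total cure secondary. Test these four in a fixed order, or by Holm, only after the primary is significant. State that recurrence and total cure are not powered. This adds no patients and matches the existing sample-size basis.

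The cost is more than wording. Four outcomes lose the primary label, and timing matters. Trial status gives recruitment from 25 March 2021 and expected completion by 24 October 2022, before the article appeared on 22 July 2023. Interim analyses also gives colorectal surgeons access to interim results. Relabelling at that stage could look like outcome switching. The change must therefore be dated, justified, and made by people without knowledge of unblinded or interim results, with that documented.

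If this is no longer possible, keep all five as primary, apply Holm across them, and report that healing time is the outcome on which the trial was sized. The price is power. If healing time had to pass at the first Holm step (0.01), its power would be about 59% with 47 per group and σ = 17.3 days.

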#### Secondary outcomes

Operation duration, hospital stay length, postoperative scar scale and days to return to work. The duration of the operation is related to postoperative complications. Long hospital stays and days to return to work indicate that patients need to pay increased operation costs.

### Safety assessment

Before the study, the following safety indicators of the patients will be measured:Laboratory tests, including routine blood tests (white blood cell count, total number of neutrophils, total number of lymphocytes, total number of monocytes, total number of eosinophils, total basophils, percentage of neutrophils, lymphocyte percentage, percentage of monocytes, eosinophil percentage, basophil percentage, total number of red cells, haemoglobin volume, erythrocyte specific volume, mean erythrocyte volume, mean erythrocyte haemoglobin content, mean erythrocyte haemoglobin concentration, erythrocyte distribution width, total platelet count, mean platelet volume, platelet distribution width and specific platelet volume); blood type (O Rh type); liver function tests (alanine transaminase and glutamyl transpeptidase); kidney function tests (serum creatinine); blood lipids; four blood coagulation indices (PT, APTT, TT and FIB); four infection diseases (antibodies of HIV, HBV, HCV and syphilis).Imageological examinations, including chest X-ray and 12-lead electrocardiography. Enteroscopy will be performed to exclude surgical contraindications.Vital signs, including blood pressure, respiration rate, heart rate, body temperature and physical examination.The safety of the two operations will be assessed on the basis of postoperative wound pain, faecal continence and wound infection. Postoperative wound pain will be rated by using the Visual Analogue Scale. In this trial, the Wexner scale will be applied to estimate anal function. Postoperative wound infection will be described by using the wound infection risk score.All adverse events occurring during the study, including mild, medium and severe impairments in patients, will be reported and recorded in detail by using a case report form (CRF).

### Participant timeline

The participant timeline is shown in Table 1.

**Table 1 Tab1:** Schedule of enrolment, interventions and assessments

Time point		Enrolment	Allocation	Operation	Check-out
Enrolment	Eligibility screening	X			
	Informed consent	X			
	Allocation		X		
Intervention	Test group			X	
	Control group			X	
Assessment	Laboratory tests	X		X	X
	Vital signs	X		X	X
	Primary efficacies			X	
	Safety indicators			X	

### Sample size

This study is a superiority trial. Our pretest showed that the average wound healing times of the graft and no-graft groups were approximately 15 and 25 days, respectively. We assume that no difference in efficacy exists among the three centres. Assuming a two-sided significance level of 0. 05 and power of 80% (*α* = 0. 05, *β* = 0. 2), the sample size is calculated as 47 (fixed model as $$n_{1} = n_{2} = \frac{{\sigma^{2} \left( {{\text{t}}_{\alpha } + t_{\beta } } \right)^{2} }}{{\delta^{2} }}$$) [11]. Considering a loss to follow-up of 10%, the sample size for each group is 52 cases, and the total is 104 cases.

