### Trial design

This randomised, double-blinded, parallel, superiority trial will be completed at three research centres, including the First Affiliated Hospital of Guangzhou University of Chinese Medicine (GZUCM), Wuyi Hospital of Traditional Chinese Medicine and Dongguan People’s Hospital, over 2 years. A total of 104 patients with low simple intersphincter anal fistulas who meet the study criteria will be randomised (1:1) to the test and control groups. The intervention will last for the whole duration of the hospital stay with a follow-up of 6 months. Informed written consent will be obtained prior to the commencement of this study. All enrolled subjects will be fully informed about the purpose, process and possible risks of the study.

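### The printed sample-size formula lacks the factor 2 for two independent groups and no SD is given, so 47 per group and 80% power are not supported as written

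*Protocol article*

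**What the plan says.** The Trial design section describes a parallel superiority trial in which 104 patients "will be randomised (1:1) to the test and control groups".

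The Sample size section of the protocol article takes its effect from a pretest: "average wound healing times of the graft and no-graft groups were approximately 15 and 25 days, respectively". It sets the error rates with "Assuming a two-sided significance level of 0. 05 and power of 80" per cent. It then states that "the sample size is calculated as 47 (fixed model as" an expression follows, which reads n1 = n2 = σ²(tα + tβ)²/δ² and is referenced to a cited source. The loss allowance comes last: "Considering a loss to follow-up of 10%, the sample size for each group is 52 cases, and the total is 104 cases".

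σ appears only as a symbol. No section of the article gives its value, says whether it is a within-group SD, or reports the size of the pretest.

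**The concern.** The label n1 = n2 shows that the expression is meant as a size per group for two separate groups. The variance of a difference between two independent means is σ²/n + σ²/n = 2σ²/n, so the size per group carries a factor 2. The printed expression is the form for one sample or for paired differences. For the same inputs it returns half the number that a two-group comparison needs.

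The missing σ makes this matter more. Means, α, power, formula and loss rate are all given, and σ is the one input left out. A reader therefore cannot tell whether the 2 was dropped in print or dropped in the calculation. The total of 104 patients rests on this paragraph, and so does the weight that a null result on healing time could bear.

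**Working it through.** **Inputs (Sample size section).** δ = 25 − 15 = 10 days; two-sided α = 0.05; power 80%; n = 47 per group before loss. σ is not stated. Normal quantiles: 1.960 + 0.8416 = 2.8016, squared 7.849.

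**Reproducing 47.** This cannot be done directly without σ. The check is to solve for the σ that yields 47.

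- Formula as printed: σ = √(47 × 10² / 7.849) = √598.8 ≈ 24.5 days.
- Factor 2 restored: σ = √(47 × 10² / (2 × 7.849)) = √299.4 ≈ 17.3 days.

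For scale, 24.5 days is about the control mean (25) and 1.6 times the graft mean (15). The 17.3 days is also above the graft mean.

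**Power of a size taken from the printed formula, σ being the within-group SD.** Put n = σ²(2.8016)²/δ² into the two-sample standard error σ√(2/n). The standardised difference becomes 2.8016/√2 = 1.981, and power is Φ(1.981 − 1.960) = Φ(0.021) ≈ 51%. σ cancels, so the result holds whatever the SD. The noncentral t at 47 per group gives 50%.

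**Size of the shortfall if the printed formula was used (σ = 24.47).**

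- Needed for 80%: 2 × 24.47² × 7.849 / 100 ≈ 94 per group.
- Difference detectable at 80% with 47 per group: 24.47 × √(2 × 7.849 / 47) = 24.47 × 0.578 ≈ 14.1 days, against the 10 days assumed.

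**Power of 47 per group over an assumed SD range** (two-sided two-sample test, δ = 10 days; the SDs are assumptions, not document figures):

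| SD (days) | Power, normal approximation | Power, noncentral t | n per group for 80%, with factor 2 | n per group, printed formula |
|---|---|---|---|---|
| 12 | 98% | 98% | 23 | 12 |
| 15 | 90% | 89% | 36 | 18 |
| 17.3 | 80% | 79% | 47 | 24 |
| 20 | 68% | 67% | 63 | 32 |
| 24.47 | 51% | 50% | 94 | 47 |

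The last two columns show the defect: the printed formula returns about half the required size at every SD. The power columns show that whether 47 is enough depends on the SD.

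**The case against.** The strongest reply is that nothing here shows 47 per group to be too few. The 24.5 days is solved backwards from 47 and is not a protocol input. It looks large beside means of 15 and 25 days, which itself suggests that the 2 may only have been lost in print. At the 17.3 days implied by the correct formula, 47 per group gives about 80%, and any smaller SD gives more. This stands. A reader might infer that the trial is underpowered, but the documents do not support that, because they give no SD.

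A second reply is that σ² might denote the variance of the between-group difference, that is, the sum of the two group variances. The printed expression would then be valid: 24.47/√2 = 17.3 days within each group, the same answer as restoring the 2. This is possible, but the article does not define σ² in that way and the cited source is not at hand.

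A third reply is that a journal article condenses its protocol. That could excuse leaving out the SD on its own. It does not excuse a printed formula that, on its usual reading, fails to give the printed power.

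Two further criticisms are tempting and do not hold. Writing tα where tα/2 is usual is not an error of substance, since the text says two-sided and tα can denote the two-sided critical value. The allowance of 52 is not a real mistake either: 47 × 1.1 = 51.7 rounds up to 52, while 47/0.9 = 52.2 rounds up to 53, a difference of one patient per group.

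**Conclusion.** The point holds as a fault in what is written. With σ as the within-group SD, the stated formula gives about 50% power for a two-group comparison, not the stated 80%, and no value or definition of σ is supplied to support 47.

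The consequence depends on which case applies. If the formula was used as printed, power at 47 per group is about 50% and about 94 per group would have been needed. If the 2 was lost in print, or σ² was the variance of the difference, the implied within-group SD is 17.3 days and power is about 79–80%. Only the pretest SD can settle this. The figures assume a common SD, a 10-day difference and a two-sided 5% test of means.

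**What to change.** Rewrite the Sample size paragraph:

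- Give the formula as 2σ²(tα/2 + tβ)²/δ² per group. If σ² was meant as the variance of the between-group difference, keep the printed form and say so.
- State the SD used, with the pretest it came from.
- Restate the power that 47 evaluable patients per group gives for a 10-day difference at that SD.

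No further enrolment is asked for. The Trial status section expected completion by 24 October 2022, before the article appeared in July 2023, so the remedy is to correct the claim. The cost is one paragraph. The restated power may be lower than 80%, or higher if the pretest SD was below about 17 days.

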### Recruitment

This RCT, in which assessors and patients are blinded, will be conducted at three research centres. The subjects in this study will be recruited from outpatient and inpatient wards by placing advertisements on social media platforms and distributing posters with details of the study and contact information in public areas of hospitals.

Patients who meet the inclusion criteria will be invited to participate in the study and provided with the details of the RCT protocol. All patients will be required to sign an informed consent form and provide complete information. The patients will be randomised (1:1) to the test and control groups. None of the patients will know about their assigned group to keep the trial blind. Then, their baseline characteristics will be assessed, and a database record will be obtained by the same colorectal surgeon. All patients will be treated with surgery and followed up on the 3rd day, 7th day, 14th day, 21st day, 28th day, 2nd month, 3rd month and 6th month postoperation. After follow-up, pictures of the wounds will be taken, and data will be evaluated.

In addition, all of the patients will be given a schedule of intervention dates and follow-up appointments. These evaluations will be performed by an assistant who will be involved neither in the randomisation nor in the treatment.

